**Figure 1 F1:**
[figure not shown]
Participant flow diagram and data collection.

### Retention strategy

Local researchers will be the main point of contact between the trial team and trial participants and will have a key role in maintaining participant engagement with the trial. They will update participant contact details, monitor for adverse events and promote progress of the trial. The trial team will visit sites prior to initiation, and run central training days where all the local researchers get to know one another, share best-practice procedures and be trained in how to carry out subsequent trial phases.

To maintain engagement with trial participants, based on suggestions from local stakeholders including young mothers, we will use vouchers for telephone airtime, birthday cards and presents for the baby, contacts from the local researcher, and use of SMS texting. High Street vouchers to the value of £25, £25 and £40 will be given after completion of the 12, 18 and 24-month interviews respectively to acknowledge their time commitment to data collection. A first year birthday gift will be sent and a second year birthday gift will be given on completion of the two year interview. Prior notification of telephone interviews will be via SMS messages to participants. A participant website will be used to encourage engagement of participants.

### Primary outcomes

Four primary outcomes are to be reported from the trial (Tables 1 and 2):

•*Birth weight (grams)*.

•*Prenatal tobacco use:* calibrated number of cigarettes per day at 34-36 weeks gestation [73];

•*Emergency attendances and/or admissions within two years of birth*: proportion of participants’ children attending Accident and Emergency (A&E) or having an emergency admission to hospital within two years of birth.

•*Second pregnancy within two years of first birth*: proportion of women with a subsequent pregnancy within two years of first birth.

### Secondary outcomes

Secondary outcomes are shown in Tables 1 and 2. Where validated scales will be used these are named and referenced; where validated scales will be modified or items selected, these are shown with a citation only; other outcome variables will be newly derived.

### Sample size estimation

A total sample of 1418 for analysis will provide at least 90% power at the two-sided 2.5% alpha level to detect differences between the two arms of 10% (40% to 30%) in the proportion having any emergency attendance or emergency admission to hospital within two years, and of 7.5% (20% to 12.5%) in the proportion with a second pregnancy within two years. For each outcome measure, the expected improvement for the FNP arm relates to a small standardised difference (approx. 0.2 or odds ratio 0.6). This small standardised difference will enable us to detect effect towards the lower end of what we expect. We will allow for a pregnancy loss of 1.5%.

We expect to obtain follow-up data for three of the four primary outcomes on at least 90% of participants by accessing the medical records in hospital and primary care for both the mother and child. Follow-up smoking rates will be collected through the late pregnancy telephone interviews. We will therefore aim to recruit a total of 1600 pregnant women to achieve our target number for analysis, as this takes into account anticipated pregnancy loss and loss to follow up.

We have chosen to use a 2.5% alpha level to allow for multiple primary outcomes within each individual population in the trial – i.e. there are two primary outcomes for the mother (smoking and second pregnancy) and two for the baby (birth weight and emergency attendances/admissions). This gives a 5% type 1 error rate for each population.

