## Background

Infants born into socioeconomic deprivation are more likely to have teenage mothers, to have been exposed to cigarette smoke during pregnancy, to have poor prenatal health profiles, and are at greater risk of adverse short-term and long-term outcomes [1-5]. In 2008 there were 44,691 live births to women under the age of 20 in England and Wales [6]. Children born to teenage mothers have lower birth weights, are less likely to be breast fed, exhibit higher mortality rates, and are more likely to suffer accidents [7]. They do worse educationally, experience more emotional and behavioural problems, and are more likely to become teenage parents themselves [8].

Over one third of infants in the UK are exposed to maternal smoking and 17% of mothers in England continue to smoke throughout pregnancy [9-11]. Maternal smoking in pregnancy impairs fetal growth - the average difference in birth weight between infants born to smokers and to non-smokers is about 250g [12]. This difference increases with the amount smoked [13]. Smoking in pregnancy increases the risk of miscarriage, premature birth, Sudden Infant Death Syndrome (SIDS), emotional and behavioural problems, cognitive problems in childhood, adolescent criminal behaviour and adult violent and non-violent crime [14-17]. Maternal smoking is also negatively associated with breastfeeding initiation and duration [18].

Eight percent of babies born in the UK are of low birth weight compared to seven percent in France and Germany [19,20]. In addition to maternal smoking, risk factors for low birth weight include being a teenage mother, infection during pregnancy (causing preterm labour), family poverty and social disadvantage [21]. Consequences of having a low birth weight for gestational age or premature delivery include neurological impairment and cognitive difficulties. Adverse consequences of low birth weight on physical health and psychological distress can be found much later on in adult life [22,23].

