***Maternal health*****&*****well-being***								
General health status (EQ-5D) [52]	***x***	***x***		***x***	***x***	***x***	***x***	
Weight / BMI (Millennium Cohort Study) [50,51]	***x***						***x***	
Psychological distress (Kessler scale) [53]	***x***						***x***	
Depression (Whooley scale) [54]				***x***	***x***	***x***	***x***	
Postnatal depression (Edinburgh PDS) [55]				***x***				
Self-efficacy (Generalised Self-efficacy Scale) [56]	***x***			***x***	***x***	***x***	***x***	
Adaptive functioning [57,58]	***x***						***x***	
Intimate partner violence (Composite Abuse Scale) [59]							***x***	

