### Statistical analysis

#### Main analysis – primary outcomes

The primary comparative analyses will be conducted on an intention-to-treat basis, with an emphasis placed on confidence intervals for differences between the randomised arms.

Descriptive statistics of demographic and outcome measures will be used to ascertain any marked imbalance between the arms at baseline. For birth weight and prenatal tobacco use at 34-36 weeks the primary comparative analyses will employ multivariable linear regression to investigate differences between the arms, adjusting for stratification/ minimisation variables. In the case of prenatal tobacco use the calibrated number of cigarettes per day reported at baseline will also be adjusted for. The result will be presented as the (adjusted) difference in mean number of cigarettes per day between the intervention and control arms. Parameter estimates will be shown alongside 95% confidence intervals (CIs) and p-values.

For the proportion of children with at least one emergency attendance and/or admission and proportion of women with known subsequent pregnancies, logistic regression will be used adjusting for stratification/minimisation variables. Comparisons will be presented as odds ratios, 95% CIs and p-values.

Multilevel modelling will be used to allow for clustering of effect within a site and Family Nurse. Where this analysis indicates little impact of clustering on effect then the results from the single level model will be presented. Sensitivity analyses will be conducted to investigate the potential impact of missing data, making different assumptions such as ‘best’ and ‘worst’ case scenarios as well as imputation models. Where variables exhibit marked imbalance at baseline, primary analyses will be repeated and adjustments will be made to check that this does not influence findings. The same analyses will be carried out for the secondary outcomes depending on the type of data.

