## Discussion

The aim of the trial is to determine whether there are important, significant differences in maternal and child outcomes during pregnancy, at birth and until the child’s second birthday between pregnant teenagers who are offered FNP and to those offered usual care in England.

Whilst there is evidence for the effectiveness of NFP from the US before the child’s second birthday, the main benefits of the NFP programme have been seen later in childhood. Therefore lack of overall programme impact cannot be concluded if this trial finds a lack of effect in the pregnancy and birth domain.

Although increased birth weight is not a direct aim of FNP, there may be an impact if rates of smoking and other lifestyle factors are influenced by the programme. Due to the clinical importance of birth weight and the availability of reliable data this has been included as a primary outcome for the child. A planned subgroup analysis of birth weight will be undertaken for mothers who smoke at baseline.

The Building Blocks randomised controlled trial has been designed to estimate impacts on outcomes occurring amongst recipients of FNP compared to routine care. As benefits of the FNP can accrue following completion of the programme, the trial includes measures which could be predictive of longer-term outcomes. At the two-year follow-up assessment (at the end of the trial), further permission will be sought to contact the trial participants to enable longer term follow-up beyond the end of the current trial period.

This trial provides an example of an evaluation of government policy. This inevitably requires management of complex interactions between a government department delivering the policy, local providers of services, locally employed researchers and university based academics. With 18 trial sites covering urban and rural settings and each with unique service provision and populations, the trial team will be required to adapt procedures and pathways to meet local need, and preserve intervention fidelity whilst maintaining the integrity of the randomised trial.

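### The primary birth-weight model leaves out baseline cigarettes per day and BMI, both collected before randomisation, and the sample size section does not say whether its 0.2 standardised difference applies to birth weight

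*Protocol article*

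**What the plan says.** **Analysis model.** Under Main analysis – primary outcomes, birth weight and prenatal tobacco use are both analysed by linear regression adjusted for the stratification/minimisation variables. One further covariate is named, for one outcome only: "In the case of prenatal tobacco use the calibrated number of cigarettes per day reported at baseline will also be adjusted for". The Randomisation section shows that smoking enters the minimisation as smoker or non-smoker, and that baseline assessments are completed before allocation. Table 1 marks tobacco use and "Weight / BMI (Millennium Cohort Study) [50,51" at baseline. Variables with marked baseline imbalance are handled by repeating the primary analysis with extra adjustment.

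**Rationale for birth weight.** The Background says "the average difference in birth weight between infants born to smokers and to non-smokers is about 250g" and that the gap widens with the amount smoked. The Discussion says that raising birth weight is not a direct aim of the programme, but "there may be an impact if rates of smoking and other lifestyle factors are influenced by the programme".

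**Planning effect.** The sample size section says: "A total sample of 1418 for analysis will provide at least 90% power at the two-sided 2.5% alpha level". It gives two contrasts, "10% (40% to 30%) in the proportion having any emergency attendance or emergency admission to hospital within two years" and "7.5% (20% to 12.5%) in the proportion with a second pregnancy within two years". It then adds: "For each outcome measure, the expected improvement for the FNP arm relates to a small standardised difference (approx. 0.2 or odds ratio 0.6"), and describes this as allowing detection towards the lower end of what is expected. It gives no birth-weight difference in grams, no birth-weight SD and no smoking rate for the trial population.

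**The concern.** The article itself says that the amount smoked matters for birth weight, and it uses the baseline amount in the tobacco model. For birth weight it keeps only the yes/no version, and it does not use BMI. Prognostic information measured before randomisation is left unused on a primary outcome for which the programme's likely effect is indirect.

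The planning sentence adds to this. A reader who takes it to cover all four primary outcomes will conclude that 0.2 SD is a cautious expectation for birth weight. A non-significant result could then be read as ruling out any effect worth having, when the smoking pathway may only produce effects well below what the trial can detect.

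**Working it through.** **Inputs from the article.** 1418 analysed, two-sided 2.5% level, at least 90% power, 1.5% pregnancy loss, 90% follow-up, 1600 recruited, 250 g gap. National smoking figures are 17% of mothers in England smoking throughout pregnancy and over one third of UK infants exposed.

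**Assumptions.** Equal allocation (709 per arm), birth-weight SD of 450 to 600 g, and extra covariates explaining a further 2 to 5% of the variance. The article gives none of these.

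**1. The plan's own figures.**
- Recruitment: 1600 × 0.985 × 0.90 = 1418.4, which matches 1418.
- Power with 709 per arm: 95.7% for 40% v 30%, 94.5% for 20% v 12.5%, 93.6% for 0.2 SD. The statement of at least 90% is true.
- Odds ratios: (0.30/0.70)/(0.40/0.60) = 0.64 and (0.125/0.875)/(0.20/0.80) = 0.57.
- Standardised differences: 0.10/√(0.35 × 0.65) = 0.21 and 0.075/√(0.1625 × 0.8375) = 0.20.

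The pair 0.2 and 0.6 therefore describes the two binary outcomes well.

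**2. Gain from the extra covariates.** The standard error is multiplied by √(1 − R²), where R² is the further share of variance explained.
- R² = 0.02: 1 − √0.98 = 1.0% smaller SE, equivalent to 1418 × (1/0.98 − 1) ≈ 29 more women.
- R² = 0.05: 1 − √0.95 = 2.5% smaller SE, equivalent to 1418 × (1/0.95 − 1) ≈ 75 more women.

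**3. Detectable birth-weight difference, 90% power.** (2.2414 + 1.2816) × 2/√1418 = 0.187 SD, or 84 g (SD 450) to 112 g (SD 600). With the extra covariates it becomes 0.185 SD (R² = 0.02) or 0.182 SD (R² = 0.05).

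**4. What 0.2 SD would require through stopping smoking alone.** 0.2 × 450 = 90 g and 0.2 × 600 = 120 g. Dividing by 250 g gives an absolute fall in smoking of 36 to 48 points across the whole arm.

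**5. Ceiling if every smoker in the programme arm stopped and no control did.**

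| Smoking rate | Shift | In SD (600 to 450 g) |
|---|---|---|
| 17% (national) | 42.5 g | 0.07–0.09 |
| one third (national) | 83 g | 0.14–0.19 |
| 40% (assumed) | 100 g | 0.17–0.22 |
| 50% (assumed) | 125 g | 0.21–0.28 |

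**6. Power for smaller illustrative falls.** Power = Φ(d√1418/2 − 2.2414) plus the opposite tail.
- 10-point fall: 25 g, power 7% (SD 600) to 12% (SD 450).
- 20-point fall: 50 g, power 25% to 44%.

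**The case against.** The planned birth-weight analysis is not wrong. Randomisation makes the estimate valid without more covariates, smoking is already adjusted for in binary form, and the gain is small and rests on an assumed R². BMI may be taken at any time up to 24 weeks and need not be a pre-pregnancy value. All this stands, and it makes the change a refinement. It does not remove the case: the article fixes this model's covariates and names a further one for tobacco only, and BMI measured before allocation is a legitimate covariate at whatever gestation it was taken.

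On the planning sentence, a reader might infer that 0.2 SD is out of reach for birth weight on the article's own 250 g figure. The document does not support that. The inference needs an SD and a trial smoking rate, and neither is given. The quoted smoking rates are national, and the Background says deprived infants, who more often have teenage mothers, are more exposed to smoke. At 50% smoking, complete cessation would exceed 0.2 SD over the whole SD range. The inference also needs a pathway through stopping alone, whereas the Discussion names other lifestyle factors and cutting down would count too. Moreover, the sentence directly follows the two binary outcomes, and an odds ratio has no meaning for a weight in grams, so it may not concern birth weight at all.

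The risk of misreading a null is partly met. The Discussion warns against concluding a lack of overall programme impact from null pregnancy and birth results, and plans a birth-weight subgroup analysis in baseline smokers; the analysis section emphasises confidence intervals. However, that warning rests on benefits appearing later in childhood and not on low power, and the article says the trial is powered for overall differences.

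**Conclusion.** The point holds as a modest improvement to the analysis and a clarification of the planning text. The primary birth-weight model leaves out two baseline variables that are already collected, one of them a dose measure that the article itself links to birth weight. Including them would cut the standard error by about 1.0 to 2.5%, on an assumed further 2 to 5% of variance explained. It would not be right to infer bias in the planned estimate.

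The 0.2 statement suits the binary outcomes. Read as covering birth weight, it is unjustified as a lower-end expectation, because nothing in the article supports a shift of 90 to 120 g (at an assumed SD of 450 to 600 g) for an outcome it calls an indirect target. That is weaker than saying such a shift is impossible. Nor does it follow that the trial is mis-sized: 1418 and 1600 reproduce, and power is at least 90% for the effects stated.

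**What to change.** - **Main analysis – primary outcomes:** pre-specify baseline calibrated cigarettes per day and baseline BMI as covariates in the primary birth-weight model, alongside the stratification/minimisation variables. Fill missing baseline values by simple imputation (for example the overall mean) without reference to arm or outcome. Keep the repeat analysis for marked imbalance as a sensitivity analysis.
- **Sample size estimation:** say which outcomes the 0.2 covers. Give the birth-weight difference detectable with 90% power at 1418 and the 2.5% level, about 0.19 SD, in grams with the assumed SD (84 to 112 g for 450 to 600 g). Note that a null result does not exclude smaller smoking-mediated effects.

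The cost is a few sentences and two covariates already being collected. No new data and no change in sample size are needed. Because the model is linear, the treatment effect remains a mean difference in grams with the same interpretation.

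### Testing both outcomes in each mother and baby pair at a fixed 2.5% is valid but needlessly conservative: Holm within each pair keeps 5% per population without losing power, and the trial-wide error rate of up to 10% should be stated

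*Protocol article*

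**What the plan says.** Under Primary outcomes the protocol article announces: "Four primary outcomes are to be reported from the trial". They are birth weight, cigarettes per day in late pregnancy, any emergency attendance or admission of the child by age two, and a second pregnancy within two years.

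Sample size estimation states the size and level: "A total sample of 1418 for analysis will provide at least 90% power at the two-sided 2.5% alpha level". Two targets are given, both for binary outcomes: a fall from 40% to 30% in children with any emergency hospital contact, and a fall from 20% to 12.5% in mothers pregnant again. For every outcome the expected effect is described as a standardised difference of about 0.2.

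The same section explains the 2.5%. Smoking and second pregnancy belong to the mother, birth weight and emergency attendance or admission belong to the baby, and alpha is divided by two within each. It concludes: "This gives a 5% type 1 error rate for each population". It gives no error rate across all four outcomes and claims none.

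**The concern.** Giving each of two outcomes a fixed 2.5% is plain Bonferroni within the pair. Once one outcome in a pair has been shown at 2.5%, the 5% for that population no longer requires the other to be held to 2.5%. A real second effect with a p-value between 2.5% and 5% would then be called non-significant with no gain in error control.

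The other matter is what a reader takes from the 5%. Both populations come from one randomisation of pregnant women and concern one programme. Four tests at 2.5% have a joint error rate near twice 5%, and the article never gives that figure. A reader who sees only the 5% may take it as the rate for the whole trial.

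**Working it through.** **Inputs.** From Sample size estimation: 1418 analysed, two-sided 2.5% per outcome, 40% v 30%, 20% v 12.5%, standardised difference about 0.2, pregnancy loss 1.5%, follow-up 90%, 1600 recruited. Assumption: 1:1 allocation, so n = 709 per arm (the article states no ratio). No clustering allowance is included.

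**1. The plan's own figures.**
- 1600 × 0.985 × 0.90 = 1418.4, which matches 1418.
- Power = Φ{[|p1−p2|√n − z√(2p̄(1−p̄))] / √(p1(1−p1)+p2(1−p2))}, with z = 2.241 at two-sided 2.5%.
- 20% v 12.5%: (0.075×26.63 − 2.241×0.5217)/0.5190 = 1.59, power 94.5%.
- 40% v 30%: (0.100×26.63 − 2.241×0.6745)/0.6708 = 1.72, power 95.7%.
- Both exceed the stated 90%.

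**2. Error per population under the fixed rule.** The bound is 2 × 2.5% = 5%; if independent, 1 − 0.975² = 4.94%. The claim is correct.

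**3. Error across the four outcomes, all null.**
- Either direction: bound 4 × 2.5% = 10%; if independent, 1 − 0.975⁴ = 9.6%. Simulation gives 9.4% at a common correlation of 0.2, 8.3% at 0.5 and 6.1% at 0.8.
- In favour of the programme only: each two-sided 2.5% test puts 1.25% in that tail. The bound is 4 × 1.25% = 5%; if independent, 1 − 0.9875⁴ = 4.9%; at correlation 0.5, 4.1%.

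**4. Error of Holm within a pair.** If both effects are null, any rejection needs the smaller p-value at or below 2.5%, so the bound is 2 × 2.5% = 5%. If one is null, it can be rejected only at p ≤ 5%, so the bound is again 5%. Two pairs give a trial-wide bound of 5% + 5% = 10%, unchanged.

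**5. Power of Holm within a pair.** Everything rejected at a fixed 2.5% is still rejected. If the outcomes are independent, power = P(p ≤ 2.5%) + P(2.5% < p ≤ 5%) × P(partner ≤ 2.5%). Power at 5% is 97.0% for second pregnancy and 97.7% for emergency attendance or admission. The partner (smoking or birth weight) at a standardised difference of 0.2 has 93.6% power at 2.5%.

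| Outcome | Fixed 2.5% | Holm, both effects real |
|---|---|---|
| Second pregnancy | 94.5% | 94.46 + 2.52×0.936 = 96.8% |
| Emergency attendance/admission | 95.7% | 95.69 + 2.03×0.936 = 97.6% |

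Follow-up for smoking comes from telephone interviews and is outside the 90% assumption, so its power may be lower. At an assumed 80%, second pregnancy still reaches 94.46 + 2.52×0.80 = 96.5%. If smoking has no effect the gain vanishes (94.5%). Whatever the correlation, the result lies between 94.5% and 97.0%.

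**6. One family of four, for comparison.** At 1.25% (Holm's first step over four), power is 92.7% (40% v 30%), 90.9% (20% v 12.5%) and 89.8% (standardised difference 0.2). With continuity correction the two binary figures are 92.0% and 89.7%. Second pregnancy needs 1378 at this level, so a design effect above 1418/1378 = 1.03 takes it below 90%.

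**The case against.** The strongest reply is that nothing here is misstated. The sentence on type 1 error is correct, names its two families and claims no trial-wide 5%. Whether mother and baby make one family or two is a judgement on which statisticians differ. All of that stands.

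Three stronger readings might be inferred, and the article does not support them.
- *The programme has a 10% chance of a false win.* The 10% counts both directions. A false result in its favour has a chance of about 5%.
- *Any single positive outcome establishes effectiveness.* The Discussion says that "lack of overall programme impact cannot be concluded if this trial finds a lack of effect in the pregnancy and birth domain". That cautions against over-reading a null result in one domain. It does not make one positive result sufficient, and no other text does.
- *All four outcomes could be controlled at 5% with 90% power kept.* This holds only for the two binary outcomes and before any allowance for clustering. A generic 0.2 difference is already at 89.8%, and multilevel modelling for site and Family Nurse is planned with no inflation in the sample size.

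It may also be said that the choice of Holm belongs in an analysis plan that is not shown, and that Holm sits less easily with interval reporting. On the first, the article itself fixes the 2.5% rule and its rationale, so the rule can be reviewed here. On the second, the Statistical analysis section already reports 95% intervals beside tests planned at 2.5%, so intervals and test level do not match under the present rule either.

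**Conclusion.** The present rule is valid but needlessly conservative. Holm within each pair keeps the 5% bound per population and the 10% bound across the trial, and cannot lose power. It gains about 2 percentage points for each outcome with a stated power target when both effects in its pair are real (94.5% to about 97%, and 95.7% to about 97.6%), and almost nothing when only one is. The gains assume 1:1 allocation, 1418 analysed, the stated effects, independence within a pair and no clustering.

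The trial-wide rate of up to 10% in either direction (9.6% if independent) is a consequence of the design that should be stated. It is not an error. Holm across all four outcomes is an optional design choice that would use up most of the power reserve. It is not a needed correction.

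**What to change.** In Sample size estimation, keep the two families and keep 2.5% as the basis for the sample size. Replace the fixed 2.5% rule with Holm within each pair: test the smaller of the two p-values at two-sided 2.5% and, if it passes, the other at two-sided 5%. Add one sentence saying that error is controlled at 5% for mother and for baby separately, and that the chance of at least one false significant difference in either direction across the four outcomes is up to 10%.

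The cost is wording only, with no extra participants and no loss of power. When one effect in a pair is real and the other null, the null outcome may be tested at 5% instead of 2.5%, which stays within the 5% already claimed for that population. If the sponsor prefers Holm over all four, any claim of at least 90% power should be confined to the two binary outcomes and marked as before clustering.
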